# EFFICHRONIC study protocol: a non-controlled, multicentre European prospective study to measure the efficiency of a chronic disease self-management programme in socioeconomically vulnerable populations

**DOI:** 10.1136/bmjopen-2019-032073

**Published:** 2019-12-18

**Keywords:** chronic disease, social determinants of health, caregivers, patient participation, self-management, cost-efficiency

## Abstract

**Introduction:**

More than 70% of world mortality is due to chronic conditions. Furthermore, it has been proven that social determinants have an enormous impact on both health-related behaviour and on the received attention from healthcare services. These determinants cause health inequalities. The objective of this study is to reduce the burden of chronic diseases in five European regions, hereby focusing on vulnerable populations, and to increase the sustainability of health systems by implementing a chronic disease self-management programme (CDSMP).

**Methods and analysis:**

2000 people with chronic conditions or informal caregivers belonging to vulnerable populations, will be enrolled in the CDSMP in Spain, Italy, the UK, France and the Netherlands. Inclusion of patients will be based on geographical, socioeconomic and clinical stratification processes. The programme will be evaluated in terms of self-efficacy, quality of life and cost-effectiveness using a combination of validated questionnaires at baseline and 6 months from baseline.

**Ethics and dissemination:**

This study will follow the directives of the Helsinki Declaration and will adhere to the European Union General Data Protection Regulation. The project’s activities, progress and outcomes will be disseminated via promotional materials, the use of mass media, online activities, presentations at events and scientific publications.

**Trial registration number:**

ISRCTN70517103; Pre-results.

Strengths and limitations of this studyComparable data on the chronic disease self-management programme implementation in five European countries with different backgrounds will be collected.The outcome of the used recruitment strategies, specifically designed for the vulnerable study population, will lead to innovative conclusions.The study is not randomised controlled to allow all possible beneficiaries to participate.One of the limitations of the study is the fact that vulnerable people, who do not speak or understand the local language, cannot be included.Ideally, a longer-term trial should be conducted to measure the outcomes at 1 year postintervention.

## Introduction

In the 21st century, chronic conditions are among the most important public health challenges mainly due to their double impact: the human suffering they cause on the one hand and the damage they produce to global socioeconomic development on the other. Even though healthcare systems are still primarily focusing on acute diseases,^1^ they are slowly transforming because of demographic changes, the increasing prevalence of chronic diseases and the budgetary crisis of recent years. This shift requires new healthcare delivery models to ensure sustainability.

Chronic conditions and also vulnerable settings^2^ are part of the 10 threats to global health the WHO has warned of recently. More than 70% of mortality worldwide (41 million people each year), is due to chronic conditions, such as cancer, diabetes, respiratory disorders and heart disease. All of them are related to five main risk factors: tobacco consumption, physical inactivity, alcohol abuse, unhealthy diet and air pollution. Furthermore, 22% of the global population lives in vulnerable settings which exist in almost all regions of the world. As a result, the 13th WHO General Programme of Work (2019–2023), expresses this concern with the slogan: ‘Promote health, keep the world safe, serve the vulnerable’, urging particularly to address health promotion in populations suffering vulnerability.^3^

The large impact of non-communicable diseases (NCDs) on national income is primarily due to loss of productivity caused by absenteeism and inability to work which threaten the sustainability of recent macroeconomic achievements. Additionally, there has been a steady global increase in healthcare expenditure on NCDs over the years. According to a systematic review on healthcare spending and national income, cardiovascular diseases account for 12% of healthcare expenditure in the European Union (EU) and diabetes-related costs were estimated at 7%.^4^ Besides, other conditions and risks factors such as depression or obesity are becoming more prevalent in higher-income EU countries and are greatly determined by poverty and low income.^5 6^

Also, recent scientific evidence has shown the enormous impact of social determinants (ie, income, unemployment, housing quality, educational level or gender) on health, which manifest in diverse short-term and long-term health inequalities.^7^ These differences are not only related to deficient self-care behaviour^1^ and poor health but also to the insufficient attention from healthcare services. Vulnerable people are generally less likely to receive preventive care, timely diagnosis or follow-up care for their chronic conditions. These observations agree with the ‘inverse care law’ theory described in 1971^8^ by Tudor Hart, referring to the fact that often, the availability of good medical or social care varies inversely with the need of the population served. This way, chronic conditions and deprivation create a vicious circle.

Fortunately, there is evidence that chronic conditions can be controlled by reducing their risk factors,^9^ which are mostly linked to unhealthy lifestyle. There is also proof that health literacy programmes that focus on self-efficacy and empowerment can successfully modify many harmful habits.^10 11^

The basis of the EFFICHRONIC project is the internationally acknowledged chronic care model^12^ which aims to promote patients’ empowerment and autonomy. The specific programme used in the project is the chronic disease self-management programme (CDSMP).^13^ It concerns a process-centred intervention constructed on the social learning theory^14^ and it is appropriate for adults living with one or more chronic conditions. Since its beginning in 1990,^15^ the effectiveness of the CDSMP has been demonstrated through positive health outcomes and more efficient use of health resources.^16^ The programme is community-focused and disseminated through an international infrastructure of training, certification and licensing.

### Study rationale

Up to date, prevention research still concentrates mainly on disease-specific interventions and few studies on particularly vulnerable populations are performed. Moreover, data on the efficiency and cost–benefit of prevention programmes are scarce, which reduces policy engagement and likewise, it prevents health systems from being more sustainable and efficient.^17 18^

EFFICHRONIC aims to empower individuals from (socially) deprived communities to manage their chronic conditions, in an integrated and non-disease specific way. The overall objective of the project is to reduce the burden of chronic conditions and increase the sustainability of health systems by implementing a CDSMP in socioeconomically vulnerable populations in five European regions.

Five specific objectives have been defined: (1) to identify vulnerable people by means of a multidimensional analysis in the involved regions; (2) to design specific recruitment strategies to reach the target population; (3) to implement the programme in the five regions with at least 400 individuals per region; (4) to generate a comprehensive impact assessment framework, including cost-efficiency and health-economic assessment; and (5) to define guidelines and policy recommendations to allow to the scaling up of the EFFICHRONIC methodology to other regions in Europe.

## Methods and analysis

### Methodology

The methodology used for the community-based intervention of EFFICHRONIC is the ‘chronic disease self-management programme’ developed at Stanford University. The CDSMP is a public health intervention provided by trained monitors. The programme is strongly evidence-based and consists of the following conceptual elements: self-efficacy, empowerment, salutogenesis, peer-to-peer education and vicarious training. It includes action planning and feedback about problem-solving skills and other competencies such as the reinterpretation of symptoms and training in disease management.

A cascade training model is used in the CDSMP method. On top are Self-Management Resource Centre licensed T-trainers possessing the maximum teaching expertise. They are in charge of training master trainers, who in their turn train monitors (or leaders) who will conduct the chronic disease self-management workshops. The monitors receive practical training on the philosophical and methodological basis of the CDSMP: empowerment, self-efficacy, group management, management of painful emotions, positive health and efficient communication among other skills. Once trained, the monitors facilitate the workshops in pairs. In each country, minimum 32 monitors will be trained to instruct the end-users: people with chronic conditions or caregivers. The CDSMP workshops last for 6 weeks with sessions of 2.5 hours once a week in groups of 12–20 participants. The programme fidelity and quality plan includes the supervision of workshops in the community by the master trainers through periodic protocolled monitor audits. Workshop assistants receive a handout with the workshop topics and homework assignments, a consultation book and a certificate of attendance if they were present at minimum 4 of the 6 sessions.

### Study design

EFFICHRONIC is a multicentre non-controlled prospective study with a duration of 3 years in five European settings: the Principality of Asturias in Spain, the area of Genoa in Italy, several regions in the UK, the Occitanic region in France and the area of Rotterdam in the Netherlands. The participating countries represent a wide range of social, economic and healthcare-related realities. The EFFICHRONIC intervention consists of the following phases: identification, recruitment and stratification of participants from vulnerable populations, implementation of the intervention and an economic and efficiency evaluation with a pre–post design. Additionally, guidelines and policy recommendations will be developed based on the project conclusions, this to allow the scaling-up of the intervention to other contexts.

### Study population

The final study population will consist of 2000 vulnerable participants distributed over the five implicated areas, who finish the CDSMP (4 out of 6 sessions) and who are evaluated 6 months after the intervention. Taking into account a drop-out rate of minimum 20%, at least 2500 participants will be recruited initially.

The vulnerability concept of EFFICHRONIC is based on a definition from the Spanish Red Cross which describes it as ‘a situation between complete social inclusion and total exclusion’.^19^ Keeping in mind this definition and adapting it to some specific requirements of the CDSMP (eg, being able to understand the local language) and of EFFICHRONIC (being traceable for follow-up at 6 months), the inclusion criteria were defined (figure 1).

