### Sample size

The study primarily wishes to demonstrate a statistically significant difference in the two subscales of the 12 items Short Form (SF-12)^20^ measuring health-related quality of life, and in the five participating countries. Based on a study on the effect of the CDSMP in lumbar back pain, the subscores ‘well-being’ and ‘energy’ of the SF-36 improved by 6.0±19.1 and 4.3±23.2, respectively, after 6 months.^21^ The lowest Cohen’s d is therefore of 0.185 in quality of life domains. Thus, the principal conclusion of the study will rely on 10 tests. Applying the Bonferroni’s correction on the significance threshold, we will consider an alpha risk of 0.005 for the tests measuring the quality of life (self-rated with SF-12) in vulnerable patients with chronic diseases and caregivers. To show a statistically significant effect size of 0.185, by a paired Student’s t-test, with a bilateral alpha risk of 0.005, a power of 0.9 and a correlation between baseline and 6 months of 0, we need to analyse 978 subjects. Assuming a drop-out rate of 20%, we need to include at least 1223 subjects. The multicentre study will include 2000 subjects (400 per country), which will bring about sufficient power to analyse the objectives.

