### Statistical analysis plan

Differences between baseline and follow-up measurements will be assessed employing the paired T-test (for normally distributed variables), the Mann-Whitney U test (for variables not normally distributed) and the Pearson χ^2^ test (for variable fractions). To adjust for multiple testing, one-way analyses of variance with post hoc testing (type Bonferroni) will be performed. The relationship of an outcome measure (T1) with explanatory variables will be determined using ordinary least squares regression analysis. The outcome measure (T0), (change in) other outcome measures, risk factors and social determinants may serve as explanatory variables. Additionally, the above-mentioned analyses will be repeated for each country separately and possibly for other subgroups (for variables which are likely to influence the effect of the intervention itself, eg, age and gender). All data from each of the five pilot sites will be anonymised and centralised at one study site for statistical analysis. Analyses will be performed with SPSS V.25.0.

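### The study population of 2000 is defined by attendance and follow-up after enrolment, so the pre–post change describes completers; other sections use 2000 for people enrolled

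*Protocol article*

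**What the plan says.** The Study population section describes the final 2000 as participants "who finish the CDSMP (4 out of 6 sessions) and who are evaluated 6 months after the intervention". It continues: "Taking into account a drop-out rate of minimum 20%, at least 2500 participants will be recruited initially". The same section says that the inclusion criteria took account of "being traceable for follow-up at 6 months".

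Other sections use 2000 differently. The Abstract gives it as the number to be enrolled in the programme. The Sample size section gives it as the number the study will include, 400 in each country, after stating "Assuming a drop-out rate of 20%, we need to include at least 1223 subjects".

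On design, the article states: "EFFICHRONIC is a multicentre non-controlled prospective study with a duration of 3 years in five European settings". The evaluation is pre–post, with a self-administered questionnaire at baseline (T0) and at 6 months (T1).

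On analysis, the Statistical analysis plan section states: "Differences between baseline and follow-up measurements will be assessed employing the paired T-test (for normally distributed variables" (the sentence goes on to name tests for other types of variable). It adds ordinary least squares regression with the T1 value as outcome. It names no analysis set.

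**The concern.** Attending four sessions and being evaluated at 6 months both happen after enrolment. A population defined by them is selected on behaviour that may be related to the outcome. In a socioeconomically vulnerable group, people may stop attending or be lost because their health worsens, because a crisis intervenes or because they see no benefit. If so, those who remain will show a better average change than the whole group would have shown.

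The analysis as described does not repair this. A paired t-test needs both measurements, and a regression on T1 needs an observed T1. The attendance condition goes further: taken literally, it removes someone who came to three sessions and returned a usable T1 questionnaire.

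The stated aims are to reduce the burden of chronic disease in vulnerable populations, to assess cost-efficiency and to support scaling up. These call for the average change among people who enter the programme. The change among those who stay is a legitimate quantity, but it answers a narrower question.

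**Working it through.** **Inputs from the article.** Study population section: 2000 completers evaluated at 6 months, drop-out of at least 20%, at least 2500 recruited. Sample size section: improvements of 6.0±19.1 and 4.3±23.2, effect size 0.185, ten tests, two-sided alpha 0.005, power 0.9, correlation 0, 978 to analyse, 1223 to include.

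**Step 1: reproduce the article's figures.**
- Recruitment: 2000 / (1 − 0.20) = 2500.
- Inclusion: 978 / (1 − 0.20) = 1222.5, rounded up to 1223.
- Effect size: 4.3 / 23.2 = 0.1853, the smaller of the two (6.0 / 19.1 = 0.314).
- Alpha: 0.05 / 10 = 0.005.
- Paired t-test with correlation 0: standardised difference 0.1853 / √2 = 0.131. The noncentral t calculation gives n = 978. With d rounded to 0.185 it gives 981.

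The stated arithmetic is sound.

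**Step 2: how many people the definition leaves out.** 2500 − 2000 = 500, or 20% of those recruited. The article calls 20% a minimum. The 500 combine people with fewer than four sessions and people without a 6-month evaluation, and the article gives no split.

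**Step 3: how far the completer figure can differ from the all-enrolled figure.** Let q be the share of non-completers, and let d_c and d_n be the standardised change in completers and non-completers.

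- d_all = (1 − q) × d_c + q × d_n
- distortion = d_c − d_all = q × (d_c − d_n)

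The documents do not give d_n. As an assumption, take d_c = 0.185 and let non-completers change by f times that amount. For f = 0 and q = 20%: 0.8 × 0.185 + 0.2 × 0 = 0.148. For f = −1: 0.8 × 0.185 − 0.2 × 0.185 = 0.111. The q = 40% column is also an assumption, shown because 20% is a floor.

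| Change in non-completers (f) | d_all, q = 20% | d_c / d_all | d_all, q = 40% | d_c / d_all |
|---|---|---|---|---|
| Gain more (1.5) | 0.204 | 0.91 | 0.222 | 0.83 |
| Same (1) | 0.185 | 1.00 | 0.185 | 1.00 |
| Half (0.5) | 0.167 | 1.11 | 0.148 | 1.25 |
| None (0) | 0.148 | 1.25 | 0.111 | 1.67 |
| Worsen by half (−0.5) | 0.130 | 1.43 | 0.074 | 2.50 |
| Worsen equally (−1) | 0.111 | 1.67 | 0.037 | 5.00 |

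**Step 4: what this means for power.** Keep the article's alpha, correlation and standard deviation. If the all-enrolled effect is 0.148, power at n = 978 falls from 0.90 to 0.68, and the number needed for power 0.9 rises from 981 to 1531. That is still below 2000.

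**The case against.** The strongest reply is that the Study population sentence is a recruitment target and not an analysis rule: the project wants 2000 finishers with follow-up and so recruits 2500. The Statistical analysis plan section does not restrict any test to people with four sessions, and a condensed article may leave analysis sets to a fuller document. This has some force. Even so, the sentence says who the final study population is, which is a stated definition and not an omission. If it is only a target, the article still uses 2000 in two senses. Clarification is needed either way.

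Several stronger inferences are tempting, and the documents do not support them.

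- **That the estimate is biased upward.** The article reports no outcomes for people who stop attending or are lost. The distortion is zero if they change equally and negative if they gain more.
- **That leavers are abandoned.** Nothing says T1 is withheld from people with fewer than four sessions.
- **That the economic analysis omits their costs.** The article mentions cost–benefit analyses but not their denominator.
- **That a control group would cure the problem.** Restricting the treated arm to attenders would still select. The lack of a control group is a separate limitation, which the article discloses and justifies.
- **That the 1223 figure shows a completer definition.** It is ordinary inflation for drop-out and mentions no attendance criterion.

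Entry rules also reduce the risk somewhat: people in a period of crisis are excluded, and traceability was considered. Neither prevents loss after enrolment.

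**Conclusion.** The point holds in limited form. The Study population section conditions the 2000 on two post-enrolment events, and the Abstract and Sample size section use the same number for people enrolled or included. On the definition as written, the pre–post change describes selected completers. Read as the change among all vulnerable people enrolled, it is probably optimistic by an unknown amount.

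A reader might conclude that the effect is certainly overstated, or by a definite 25% or 67%. The documents do not support that. Those percentages hold only if 20% are non-completers, completers change by 0.185, and non-completers respectively do not change or worsen by 0.185. That optimism is likely is a judgement: it rests on the view that people who leave tend to do worse.

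The change is cheap and worth making while follow-up is still possible, because T1 questionnaires not sought at the time cannot be recovered later.

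**What to change.** In the Study population section, make the primary analysis set everyone enrolled who completed the T0 questionnaire, whatever number of sessions they attended. Then:

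1. Send the self-administered T1 questionnaire to all of them, and keep every T1 returned by people with fewer than four sessions.
2. Report participants with at least four sessions as a secondary analysis, labelled as completers.
3. Handle missing T1 under a stated assumption. A mixed model on T0 and T1 is reasonable as a starting point, but it relies on missing at random and will not remove bias from loss caused by worsening after baseline. Add sensitivity analyses that set missing changes to no change and to worsening.
4. State that the economic analysis counts everyone who starts the programme.
5. Give 2000 one meaning in the Abstract, Study population and Sample size sections, and state separately how many are to be recruited, to complete the programme and to be evaluated.

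The cost is the revised wording and some extra follow-up. With 20% loss, up to about 500 people are involved, but some of these will already have been sent T1 and some will not be reachable. The estimated effect will probably be smaller.

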**Figure 1 F1:**
[figure not shown]
EFFICHRONIC: inclusion criteria flowchart. MPI, Multidimensional Prognostic Index; NGO, non-governmental organisations.

The target population involves two main groups: vulnerable people with at least one chronic condition, and informal caregivers who are socially isolated. In general, participants must be minimum 18 years old, reside in the selected geographical areas, have their basic housing needs met and possess adequate knowledge of the local language.

Participants with chronic conditions are either people older than 65 living alone or in a nursing home; people having difficulties to make ends meet (especially if belonging to an ethnic minority or being a legal immigrant, asylum seeker or refugee); or people who are imprisoned. A chronic disease, self-reported or clinically evaluated, is outlined as a pathology listed in the International Classification of Primary Care (ICPC-2) with a code between 70 and 99 in 1 of the 17 chapters and should have >6 months of evolution.

Informal caregivers are defined as people looking after a sick person, usually a relative, without receiving payment. Additionally, to be included in the study, it is required that they are socially isolated, as is the case of carers living in remote areas without transportation or with limited access to it (without a private car and public transport at >1 km from the house), without internet access or little social support.

General exclusion criteria are: going through a period of crisis (eg, being evicted), having severe mental health problems that cause a distorted perception of reality and/or inability to participate in group dynamics, having cognitive decline (eg, Alzheimer’s) or having active addictive disorders. Although the excluded groups are among the most vulnerable of society, they need other and more specific interventions before being eligible for a self-management programme.

